### **9.2.5 Assessments in participants who prematurely stop the study**

Patients who choose to withdraw from the study during the treatment intervention will be considered as drop-outs. Patients who choose to withdraw from the study during the follow-up period (i.e. refuse to participate in the telephone interviews on days 35, 90, and 180 or to come to the outpatient visit on day 35, if applicable) will be asked for permission to contact their treating physician for inquiry of the 1° outcome and to use their data collected so far. This will prevent their drop-out. If patients do not permit the inquiry of the 1° outcome, their data will be considered right-censored from the last documented contact onward.

## **9.3 Procedures at each visit**

### **9.3.1 Screening visit (visit 1)**

Evaluate for eligibility according to inclusion and exclusion criteria. Obtain informed consent. Measure height and weight. Perform urine pregnancy test if appropriate (in menstruating women). Schedule visit 2.

### **9.3.2 Day 1 (visit 2)**

Measure heart rate and blood pressure in recumbent and supine position after at least 5 minutes resting. Randomize patient. Perform 250 mcg Synacthen® test. Draw blood for reserve serum. For reserve serum: centrifuge sample, pipet serum into 1 ml aliquots, store at -20°C. Assess VAS for general health status. Fill out CRF. Dispense trial medication. Schedule visit 3.

### **9.3.3 Day 7 ± 1d (visit 3)**

A. Telephone interview: Assess VAS for general health status. Fill out CRF. Ask patient about pill count. Schedule visit 3.

B. Clinical visit (subgroup of 180 patients living near their respective trial site): Measure heart rate and blood pressure in recumbent and supine position after at least 5 minutes resting. Perform 250 mcg Synacthen test. Draw blood for reserve serum. For reserve serum: centrifuge sample, pipet serum into 1 ml aliquots, store at -20°C. Schedule visit 4.

### **9.3.4 Day 28 ± 3d (visit 4)**

Telephone interview: Assess VAS for general health status. Fill out CRF. Ask patient about pill count at termination of trial medication, ask patient to send back spare study tablets or bring them along if a clinical visit is planned on day 35. Schedule visit 5.

### **9.3.5 Day 35 ± 3d (visit 5)**

A. Telephone interview: Assess VAS for general health status. Fill out CRF. Schedule visit 6.

B. Clinical visit (subgroup of 180 patients living near their respective trial site): Measure heart rate and blood pressure in recumbent and supine position after at least 5 minutes resting. Perform 250 mcg Synacthen test. Draw blood for reserve serum. For reserve serum: centrifuge sample, pipet serum into 1 ml aliquots, store at -20°C. Schedule visit 6.

### **9.3.6 Day 90 ± 5d (visit 6)**

Telephone interview: Assess VAS for general health status. Fill out CRF.

### **9.3.7 Closeout visit Day 180 ± 7d (visit 7)**

Telephone interview: Assess VAS for general health status. Fill out CRF.

## 10. SAFETY

### 10.1 Drug studies

During the entire duration of the study, all serious adverse events (SAEs) are collected, fully investigated and documented in source documents and case report forms (CRF). Study duration encompasses the time from when the participant signs the informed consent until the last protocol-specific procedure has been completed, including the follow-up period of six months.

#### 10.1.1 Definition and assessment of serious adverse events and other safety related events

A Serious Adverse Event (SAE) is defined as any of the following:

Hospitalization, death, life-threatening incident, persistent disability, or other medically important condition.

Both Investigator and Sponsor-investigator make a causality assessment of the event to the study drug, based on the criteria listed in the ICH E2A guidelines:

| Relationship                                                                            | Description                                                                                                               |
|-----------------------------------------------------------------------------------------|---------------------------------------------------------------------------------------------------------------------------|
| Definitely                                                                              | Temporal relationship
Improvement after dechallenge*
Recurrence after rechallenge
(or other proof of drug cause) |
| Probably                                                                                | Temporal relationship
Improvement after dechallenge
No other cause evident                                          |
| Possibly                                                                                | Temporal relationship
Other cause possible                                                                             |
| Unlikely                                                                                | Any assessable reaction that does not fulfil the above conditions                                                         |
| Not related                                                                             | Causal relationship can be ruled out                                                                                      |
| *Improvement after dechallenge only taken into consideration, if applicable to reaction |                                                                                                                           |

In agreement with the new law on clinical research (ordinance ClinO), "adverse events" are not documented; however, potential side effects of glucocorticoids (cf. section 9.2.4.1 above) are assessed and recorded on the CRF.

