#### 3.2 Investigational Product (treatment, device) and Indication

Standard treatment arm: Prednisone, a synthetic glucocorticoid with intermediate duration of action (biological half-life 18-35 hrs). The detailed characteristics of the compound, marketed under several brand names, can be found at [www.swissmedicinfo.ch](http://www.swissmedicinfo.ch): Prednison Streuli (Swissmedic registration number: 29349); Prednison Axapharm (Swissmedic registration number: 58761); Prednison Galepharm (Swissmedic registration number: 50821). In Germany, the compound is also marketed under several brand names, e.g. Prednison Galen (registration number for 5 mg strength: 33644.00.00), Prednison Decortin (registration number for 5 mg strength: 8452.00.00), or Prednison Acis (registration number for 5 mg strength: 49572.00.00).

Interventional treatment arm: matching placebo.

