### 5.2 Secondary Outcomes

1. Time to first occurrence of individual components of the primary outcome;
2. Cumulative overall systemic glucocorticoid dose;
3. Cumulative systemic glucocorticoid dose administered to treat or prevent adrenal failure;
4. Cumulative systemic glucocorticoid dose administered to treat relapse of disease, specified for each disease;
5. General health status as self-assessed by the participant on a visual analog scale (VAS) from 0 to 100, assessed at days 1, 7, 28, 35, 90, 180;
6. Score of symptoms and signs of hypocortisolism: weakness, hypothermia, nausea, vomiting, abdominal pain, fatigue, dizziness (assessed in structured interviews at time points: days 1, 7, 28, 35, 90, 180). Blood pressure (supine and standing) is assessed day 1 in all participants, but due to limited resources only in a subgroup of 180 patients living near their respective study center on days 7 and 35.
7. Performance in 250 mcg ACTH (Synacthen®) test: test assessed day 1 in all participants, plus days 7 and 35 in a subgroup of 180 patients,
8. In patients hospitalized at study entry: length of hospital stay.

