## 7. STUDY POPULATION

### 7.1 Eligibility criteria

Both in- and outpatients are eligible. Outpatient participants may be followed in specialty clinics or by general practitioners in their practice. Inpatient participants may be hospitalized on organ-specific or on general internal medicine wards of the participating trial sites (see p. 12, paragraph 1.2).

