## **8. STUDY INTERVENTION**

### **8.1 Identity of Investigational Products (treatment / medical device)**

Study drug: prednisone vs. matching placebo.

1. Standard (tapering) arm: patients receive 7.5 mg prednisone/d for 7 days; then 5 mg prednisone/d for 7 days; then 2.5 mg prednisone/d for 7 days; then 2.5 mg prednisone every other day for 7 days, then stop.

2. Intervention (abrupt stop) arm: patients receive matching placebo for 4 weeks, then stop.

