#### Suspected Unexpected Serious Adverse Reactions (SUSARs)

The Sponsor-Investigator (Chief Investigator) evaluates any SAE that has been reported regarding seriousness, causality and expectedness. If the event is related to the investigational product and is both serious and unexpected, it is classified as a SUSAR.

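### SAE relatedness and SUSAR status are tied to the study drug, which is placebo in the abrupt-stop arm, and prolongation of an existing hospital stay is not a listed SAE criterion

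*Protocol*

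**What the plan says.** **Causality.** Protocol Section 10.1.1 sets one object for the assessment: "Both Investigator and Sponsor-investigator make a causality assessment of the event to the study drug". The scale runs from *definitely* to *not related* and is built on timing, dechallenge, rechallenge and the absence of another cause. A footnote says that dechallenge counts only where it applies to the reaction.

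**SUSARs.** The SUSAR paragraph of the same section reads: "If the event is related to the investigational product and is both serious and unexpected, it is classified as a SUSAR".

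**The product.** Section 8.1 defines it: "Study drug: prednisone vs. matching placebo". For the experimental arm it says: "Intervention (abrupt stop) arm: patients receive matching placebo for 4 weeks, then stop". Section 3.2 agrees: "Interventional treatment arm: matching placebo".

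**Seriousness.** The SAE definition in Section 10.1.1 is this list: "Hospitalization, death, life-threatening incident, persistent disability, or other medically important condition".

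**Inpatients.** Section 7.1 admits them: "Both in- and outpatients are eligible". Section 5.2 makes their stay a secondary outcome: "In patients hospitalized at study entry: length of hospital stay".

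**The concern.** The trial asks whether stopping glucocorticoid abruptly is safe. The harm of interest therefore comes from taking a drug away, whereas the safety rules are written for a harm that comes from giving one. An assessor who follows the wording asks whether the tablet caused the event. For a patient on placebo, the literal answer is no, even if the abrupt stop did cause it.

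Relatedness coding and expedited reporting are at stake. Under Section 10.1.2, SUSAR status triggers immediate notice to authorities and ethics committees, and it is the only stated trigger for alerting the other local investigators.

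The second gap concerns patients already in hospital at entry. If weakness, hypotension or flare keeps such a patient in longer, there is no new admission. The listed hospitalization criterion then does not plainly apply, in the period just after the stop when the arms differ most in treatment.

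**Working it through.** The point rests on the text, so the check sets the sections side by side.

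1. **Object of the assessment.** Section 10.1.1 names the study drug, and its SUSAR paragraph names the investigational product. Nothing in Section 10 says that either term includes the act of stopping or tapering.

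2. **What that object is.** By Sections 3.2 and 8.1 it is prednisone in the taper arm and placebo in the abrupt-stop arm.

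3. **Where the named harms come from.** Section 3.7 gives flare-up, glucocorticoid deficiency and withdrawal syndrome as the risks of the placebo arm. All three follow from ending the earlier glucocorticoid, and none from the tablet. Sections 4.2 and 4.4 make the safety of rapid termination the primary and the safety objective.

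4. **Applying the scale to a withdrawal event in the abrupt-stop arm.**
   - Literal reading: placebo did not cause it, so it is unrelated.
   - Broad reading, with study drug taken to mean the allocated regimen: the timing fits. With dechallenge set aside under the footnote, *probably* needs only that no other cause is evident, and *possibly* needs only that another cause is possible.
   - The text does not choose between these readings, so two sites can code the same event differently.

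5. **SUSAR conditions.** The event must be related, serious and unexpected. The literal reading fails the first condition. The broad reading can meet it, but the third remains open: the protocol itself foresees these risks (Section 3.7) and names adrenal crisis as an endpoint (Section 5.1).

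6. **Applying the SAE list to a prolonged stay.** Take an inpatient at randomization who deteriorates without dying.
   - Hospitalization: there is no new admission, and prolongation is not mentioned.
   - Life-threatening incident or persistent disability: only if the event is that severe.
   - Other medically important condition: a matter of judgement.
   - Section 10.1.1 cites ICH E2A for the causality criteria, not for the seriousness criteria, so that reference does not supply the missing item.

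7. **What else would record it.** The AE list in Section 10.1.2 consists of prednisone side effects, does not include hypotension, and has an optional free-text field. After day 1, blood pressure is scheduled only in the subgroup of 180 (Section 9.2.4.3). Hypocortisolism symptoms and length of stay are secondary outcomes (Section 5.2).

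8. **Where the gap carries forward.** Section 11.4.5 bases DSMB reports on safety outcomes, with reference to Section 10, and on event types and relevance as defined for SAEs.

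9. **Numbers.** With 573 patients randomized 1:1, 573 / 2 = 286.5, so about 286 fall in the arm where the product is placebo. The inpatient share is not stated. At an assumed 10% to 40%, 573 x 0.10 = 57 and 573 x 0.40 = 229 patients would be in hospital at entry. These are patients to whom the wording applies, not misclassified events. The protocol gives no rate from which to estimate those.

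**The case against.** The strongest reply is that little depends on the coding, and much of it stands.

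- **Collection does not depend on causality.** All SAEs are collected (Section 10.1) and reported to the sponsor-investigator (Section 10.1.2). The components of the primary outcome are safety outcomes (Section 5.4) and are summarised by arm at the end. The DSMB may request data by arm (Section 11.4.5).
- **SUSARs are not the only route out.** Section 10.1.2 also provides for informing authorities and ethics committees of SAEs under local requirements, for reporting deaths within 7 days, and for annual safety reports.
- **Assessors are blinded** (Section 6.2.2). Unless the code is broken under Section 6.3, they do not know that the tablet is placebo and may well choose *possibly*. No section says that *possibly* counts as unrelated.
- **Inpatients have other safeguards.** Unplanned glucocorticoid therapy or adrenal crisis in an inpatient is still a primary event.

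Three stronger readings may tempt a reader, and the protocol does not support them. The first is that a withdrawal event can never be graded *probably* or *definitely*. The footnote sets dechallenge aside where it does not apply, and *definitely* accepts other proof in place of rechallenge. The second is that a prolonged stay is excluded from the SAEs. It is only not listed, and can enter through another criterion. The third is that rewording would turn these events into SUSARs. Some may be expected, and the reference safety information is not in the protocol.

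The reply does not remove the two gaps. The footnote changes the evidence required, not the object being judged, and the seriousness of a prolonged stay still depends on individual judgement.

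**Conclusion.** Both gaps are real and worth closing. Neither undermines the trial.

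- **Relatedness.** The object of the causality assessment does not match the intervention. Followed literally, withdrawal harms in the abrupt-stop arm can be coded as unrelated or coded inconsistently, and can fail the relatedness condition for a SUSAR.
- **Prolongation.** Deterioration that lengthens an existing stay may be missing from SAE counts and DSMB reports, because its entry depends on another criterion or on judgement.

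The effect falls on relatedness coding, expedited reporting and SAE counts among inpatients. A reader might infer that the harm under study is lost to the analysis. It is not, because the main between-arm comparison is largely protected by collection regardless of causality and by the summary of primary-outcome components by arm. The number of events affected cannot be estimated from the protocol. The conclusion assumes that no other trial document, such as the SAE form, already defines relatedness to include withdrawal or seriousness to include prolongation.

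**What to change.** 1. In Section 10.1.1, have causality assessed against the allocated strategy (stopping or tapering of glucocorticoid) as well as against the study drug.
2. Use the same relation in the SUSAR paragraph, and leave the seriousness and expectedness conditions as they are.
3. Add prolongation of an existing hospitalization to the SAE definition.
4. Check that the SAE form in SecuTrial carries the same wording. The form is not part of the protocol text.

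The cost is a few wording changes and perhaps one form field, with somewhat more SAE reports, and possibly more SUSAR reports, to process. Treatment, the primary outcome and the sample size are unaffected.

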#### Suspected Unexpected Serious Adverse Reactions (SUSARs)

The Sponsor-Investigator (Chief Investigator) evaluates any SAE that has been reported regarding seriousness, causality and expectedness. If the event is related to the investigational product and is both serious and unexpected, it is classified as a SUSAR.

#### 10.1.2 Reporting and documentation of Serious Adverse Events (SAE), Adverse Events (AEs), and other safety related events

All SAEs are reported by the local investigator via the electronic form supplied in SecuTrial to the Sponsor-Investigator of the study immediately after obtaining knowledge. The Sponsor-Investigator automatically receives an immediate notification by E-mail after the SAE form has been completed electronically. He will evaluate the SAE and discuss it with the local staff if deemed necessary. The electronic SAE form may then be amended by the local team, which will create another automatic E-mail to the Sponsor-Investigator. Ongoing SAEs are followed up and reported via SecuTrial until their end.

In addition to the electronic documentation via SecuTrial, all SAEs are documented in paper form, signed by the local staff, and filed in the Trial Site File.

The Sponsor-Investigator (Chief Investigator) is responsible for informing all competent authorities (CA) and ethical committees (CEC) of the concerned Member States of any Serious Adverse Events as per local requirements-

SAEs resulting in death are reported to the local Ethics Committee in Switzerland and Germany within 7 days. The other Ethics Committees involved in the trial receive SAEs resulting in death in Switzerland via Sponsor-Investigator within 7 days.

#### Documenting of AEs

These are documented in SecuTrial as prednisone side effects and include the following: infection, allergic reactions, arterial hypertension, hyperglycemia, psychic symptoms (mood changes, depression, productive symptoms), arterial hypertension, gastrointestinal ulceration, osteoporosis, aseptic bone necrosis, nausea, weight gain, atrophic changes or easy bruising of the skin, erythema, muscle weakness. Additional AE information may be documented in a free text field in SecuTrial.

#### Reporting of SUSARs

All SUSARs are reported by the local investigator via the electronic form supplied in SecuTrial to the Sponsor-

---

Investigator immediately after obtaining knowledge. The Sponsor-Investigator will report all SUSARs in compliance with applicable laws and regulations to all Competent Authorities of the concerned Member States (e.g. the BfArM in Germany, Swissmedic in Switzerland, and CECs of all study sites (lead CEC in Switzerland) immediately after obtaining knowledge.

In addition, the Sponsor-Investigator (Chief Investigator) must inform all local Investigators participating in the clinical study of the occurrence of a SUSAR.

Reporting of Safety Signals

n.a.

Reporting and Handling of Pregnancies

n.a.

Periodic reporting of safety

An annual safety report is submitted once a year to the Competent Authorities and CECs of all study sites (lead CEC in Switzerland and Germany)- by the Sponsor-Investigator.

**10.1.3 Follow up of Serious Adverse Events**

Participants with an SAE will be followed up until the SAE has resolved or the patient is lost to follow-up. If a patient with an SAE wishes to leave the study prematurely, he/she will be asked permission to assess the primary outcome parameters by obtaining the information from the treating physician. If a participant is lost to follow-up but has not expressed the wish to leave the study prematurely, the treating physician will be contacted to assess the primary outcome.

If a participant has an SAE ongoing beyond the regular time point of study termination, i.e. day 180, the SAE will nevertheless be followed until its resolution (or the loss of follow-up), including the cumulative the dose of prednisone-equivalent administered to treat the event.

---

## 11. STATISTICAL METHODS

### 11.1 Hypothesis

The aim of the trial is to test the hypothesis that rapid termination of glucocorticoid treatment (experimental arm) is noninferior to the tapering regime (control arm) with regard to the time to event (primary composite outcome). Accordingly, the null hypothesis corresponds to inferiority of the abrupt glucocorticoid tapering regime.

### 11.2 Determination of Sample Size

To assess the primary outcome measure, a Cox proportional hazards regression model will be fitted to the data. Non-inferiority will be concluded if the two-sided 95% confidence interval of the hazard ratio between the experimental and the control arm lies entirely below the critical hazard ratio defined as

$$HR = \frac{\lambda_e}{\lambda_c} = \frac{\frac{-\log(\pi_{et})}{t}}{\frac{-\log(\pi_{ct})}{t}} = \frac{\log(\pi_{et})}{\log(\pi_{ct})} = \frac{\log(\pi_{ct} - m)}{\log(\pi_{ct})}$$

where  $\lambda_e$  and  $\lambda_c$  are the hazard rates in the experimental and control arms,  $t$  is a fixed point of time,  $\pi_{et}$  and  $\pi_{ct}$  are the proportions of event-free patients at time  $t$ , and  $m$  is the non-inferiority margin expressed as the additional proportion of patients having had an event in the experimental arm, assuming that the occurrence of events follows an exponential distribution. Noninferiority will be concluded if the upper limit of the two-sided 95% confidence interval of the hazard ratio lies below the critical hazard ratio.

For the sample size estimation, the following assumptions were made:

- Patients are randomized to the control and experimental arms in a 1:1 ratio.
- After inclusion, all patients are followed for 6 months. Patients without an event within 6 months are considered right-censored and are not followed any further even though the trial might be ongoing.
- 10% of patients drop out within the 6 months follow-up period. The drop-out events are distributed uniformly over this period.
- The event rate within the 6 months follow-up period, i.e., the proportion of patients with an event, is 40%, both for the control and the experimental arms. We estimated this overall figure based on expected relapse rates for the various eligible diseases, as indicated by clinical experts and published data, e.g. in COPD or inflammatory bowel disease. Our estimation is conservative since the other components of the combined primary outcome will contribute to the event rate.
- The survival curves in the control and experimental arms follow the same exponential distribution. The rate parameter of the exponential distribution is chosen so that the corresponding cumulative distribution function value at 6 months equals the assumed event rate.
- The non-inferiority margin is defined as an absolute increase of the event rate by 13% over 6 months. We used a modified Delphi approach to determine this margin. 10 experienced clinicians board-certified in internal medicine and/or rheumatology, gastroenterology, and endocrinology were individually asked to define the maximum increase in outcome events they would accept for the benefit of rapid glucocorticoid stop and gain of high-quality scientific data in the area of steroid withdrawal. Assuming an event rate of 40% in the standard treatment arm, the mean tolerable increase under experimental treatment was 13.6% (range, 5 to 20%; median, 13%).
- The significance level is 5%.

For each combination of the noninferiority margins 7.5%, 7.6%, ..., 17.5%, and the sample sizes  $n = 200, 210, \dots, 1200, 999$  individual data sets were simulated based on the above assumptions. A Cox proportional hazards regression model was fitted to each data set, and the hazard ratios for the experimental vs. the control arm with the associated 95% confidence interval were estimated. Noninferiority was concluded if the upper limit of the two-sided 95% confidence interval of the hazard ratio was below the critical hazard ratio (see above equation). The power was estimated as the proportion of positive conclusions divided by the total number of the 999 iterations per parameter combination. To achieve a power of 80%, 573 patients (95% CI, 565 to 580) need to be included, assuming an event rate of 40% over the 6 months follow-up period and setting the non-inferiority margin to 13% (Figure). The critical hazard ratio for this noninferiority scenario is 1.478.

The sample size of  $n=573$  is a conservative estimation, since the assumed drop-out rate of 10% is relatively high.

[figure not shown]

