#### 11.4.2 Primary Analysis

A Cox proportional hazards regression model with time to the (combined) primary endpoint as the response and treatment arm as the explanatory variable will be fitted, stratified after study centre, prednisone dose, and age group. Non-inferiority will be concluded if the two-sided 95% confidence interval of the hazard ratio (HR) between the experimental and the control arm lies entirely below the critical HR ratio of 1.478. The analysis will be conducted on the PP set.

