#### **11.4.4 Interim analyses**

Once 70% of the planned sample size will have their primary endpoint assessed, we will perform a blinded, pooled, sample size re-estimation. To this end, the global rate of events – pooled over both treatment arms – will be calculated, and compared to the assumed rate in the sample size estimation. The sample size estimation will be repeated as performed originally and the study's sample size adjusted accordingly in case more patients are needed. In no case will the originally calculated sample size be reduced.

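### The stated sample size of 573 (565 to 580) does not follow from the stated uniform drop-out, which needs about 540 to 550 patients; the mismatch is conservative, but the 70% re-estimation would repeat it

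*Protocol*

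**What the plan says.** Section 11.2 lists the inputs of a simulated sample size:

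- The six-month risk is the same in each arm: "the proportion of patients with an event, is 40%, both for the control and the experimental arms". Survival in both arms follows one exponential distribution that reaches this risk at six months.
- "The non-inferiority margin is defined as an absolute increase of the event rate by 13% over 6 months", which the section converts to a critical hazard ratio of 1.478.
- Ten per cent of patients drop out within six months. "The drop-out events are distributed uniformly over this period".
- Allocation is 1:1 and follow-up is fixed at six months.
- A Cox model was fitted to each simulated data set. "Noninferiority was concluded if the upper limit of the two-sided 95% confidence interval of the hazard ratio was below the critical hazard ratio".

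The result is: "To achieve a power of 80%, 573 patients (95% CI, 565 to 580) need to be included". The section calls 573 conservative because a 10% drop-out rate is relatively high.

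Two later sections bear on this. Section 11.4.2 plans the primary Cox model "stratified after study centre, prednisone dose, and age group"; no strata appear among the simulation assumptions in Section 11.2. Section 11.4.4 provides a blinded, pooled re-estimation once 70% of the planned sample has its endpoint assessed: "The sample size estimation will be repeated as performed originally". It allows an increase and rules out a reduction.

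**The concern.** A patient who drops out at a time spread evenly over six months is at risk until then and can have a counted event first. Such patients give fewer events than completers, but not none. Dividing the completers' sample size by 0.90 treats them as giving none, and 573 is what that division produces. If so, the text describes one drop-out model and the number comes from another.

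The described simulation also fits a simpler model than the one planned. A stratified Cox model compares patients only within their stratum, so small strata can lose information.

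What is at stake is mainly the re-estimation. Someone who follows the written assumptions and someone who re-runs a calculation that gives 573 would reach sample sizes about 5 to 6% apart from the same pooled event rate. That choice should be settled before the pooled rate is seen.

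**Working it through.** **Inputs** (all from Section 11.2): risk 0.40 in each arm; margin 0.13; two-sided 95% limit; power 80%; 1:1 allocation; drop-out 10%, uniform over six months; exponential event times.

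1. **Critical hazard ratio.** log(0.60 − 0.13) / log(0.60) = log(0.47) / log(0.60) = 1.478. This matches the protocol.

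2. **Events needed** (Schoenfeld, true hazard ratio 1). 4 × (1.960 + 0.842)² / (ln 1.478)² = 205.7, so 206.

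3. **Reproducing 573.** 206 / 0.40 = 515 patients without drop-out; 515 / 0.90 = 572.2, so 573. This is an exact match. It counts drop-outs as giving no events. Simulating it that way at 573 gave 206 events on average and 79.6% power (6,000 data sets).

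4. **The stated drop-out, read as 10% assigned a uniform leaving time.** With time in units of six months the hazard is −ln(0.60) = 0.5108. The chance of an event before a uniform leaving time is 1 − 0.40 / 0.5108 = 0.217. Overall event probability: 0.90 × 0.40 + 0.10 × 0.217 = 0.3817. N = 206 / 0.3817 = 540.

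5. **The stated drop-out, read as 10% seen to leave before any event.** The share assigned a leaving time must be 0.10 / (1 − 0.217) = 0.1277. Overall event probability: 0.8723 × 0.40 + 0.1277 × 0.217 = 0.3766. N = 206 / 0.3766 = 547.

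6. **Power at 573 under step 4.** Expected events: 573 × 0.3817 = 218.7. By the Schoenfeld formula the power is 82.4%.

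7. **Simulation check** (unstratified Cox, 6,000 data sets per row, error about 0.5 points):

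| Drop-out | N | Mean events | Power |
|---|---|---|---|
| Uniform, 10% assigned | 540 | 206 | 79.7% |
| Uniform, 10% assigned | 573 | 219 | 81.5% |
| Uniform, 10% observed | 540 | 203 | 79.4% |
| Uniform, 10% observed | 573 | 216 | 81.7% |
| No events from drop-outs | 573 | 206 | 79.6% |

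A further set of 8,000 trials per size, with the 10% assigned a uniform leaving time, gave 79% at 540, 81% at 550 and 82% at 573. Under either reading, 80% is reached at about 540 to 550.

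8. **Other formulas.** Exponential drop-out gives 540. Freedman's formula needs 211 events, hence 211 / 0.3817 = 553 with uniform drop-out and 211 / 0.40 / 0.90 = 586 with simple inflation. None of these falls within 565 to 580.

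9. **Stratified Cox at 573 with uniform drop-out.** The number of strata is not in the text. The runs below assume equal strata, near-balanced arms within strata and no differences in risk between strata (3,000 data sets each, error about 0.7 points):

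| Strata | 8 | 20 | 32 | 40 | 60 | 80 | 120 |
|---|---|---|---|---|---|---|---|
| Power | 80.9% | 82.3% | 81.3% | 81.0% | 80.8% | 78.3% | 76.7% |

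Looser balance brings the loss earlier. With a 70% biased coin within strata and an assumed 4 to 6 dose-by-age cells per centre, power was 80–81% for 5 to 10 centres, 77–80% for 15 and 75–78% for 20. With no balancing at all, a cruder check gave 77% at 60 strata.

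**The case against.** The best defence is that 573 does follow from a natural reading. In a time-to-first-event analysis, a patient who has had the event is complete, so a drop-out is someone censored without one. If 10% of patients are made event-free and censored at uniform times, simulated power is 78.9% at 560, 79.5% at 572 and 79.6% at 580 (error about 0.45 points), which is compatible with 573 for 80%.

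This explains where the number may come from, but it does not remove the mismatch. The section gives all patients in both arms the same exponential curve. Patients at risk on that curve until a uniform leaving time cannot be event-free by construction. When drop-outs are defined as those seen to leave without an event and the curve is kept, the answer is 547 (step 5), not 573.

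The rest of the defence stands. The discrepancy makes the trial slightly larger than needed. The decision rule and the critical hazard ratio are unaffected. Sizing a trial with a simpler model than the analysis model is common. The handling of small centres may be settled in an analysis plan that is not at hand.

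**Conclusion.** The stated drop-out assumption and the stated sample size disagree. The listed assumptions need about 540 to 550 patients, outside 565 to 580, and 573 gives about 82% power unstratified (81.5% to 82.4%). By the formulas the excess is 573 − 547 = 26 to 573 − 540 = 33 patients. The protocol's interval extends only about 7 or 8 patients either side of 573, so simulation error does not explain it. The result rests on the protocol's own inputs and on keeping its exponential curve for every patient.

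Three stronger conclusions might be inferred, and the documents do not support them:

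- **That 573 is too small or unexplained.** It is the ordinary inflated figure and exceeds what the stated assumptions need.
- **That 573 fails under the stratified model.** Centre, dose and age category counts are not in the text. With near-balanced equal strata, power stays at about 80% or more up to about 60 strata. It falls below only with many small strata or looser balance. What can be said is that the described simulation names no strata, so it does not show the power of the planned analysis.
- **That the re-estimation puts power at risk through the drop-out handling.** That handling can only overstate the size needed, and Section 11.4.4 rules out a reduction. Leaving out strata could work in the other direction, by an amount that cannot be fixed from the text.

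This is a reporting inconsistency of modest size, worth settling because Section 11.4.4 commits to repeating the calculation.

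**What to change.** Keep 573.

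1. In Section 11.2, choose one of two corrections. Either state that drop-outs were counted as giving no events, in which case 573 and its interval can stand with the uniform-timing sentence clarified. Or correct the drop-out coding and restate the power (about 82% unstratified at 573) and the interval.
2. Say in the same section whether the simulation used strata.
3. In Section 11.4.4, replace the commitment to repeat the original calculation. Before the 70% look, fix code that uses the drop-out assumption as then stated and the planned stratified Cox model with the actual stratum counts.

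The cost is a re-run of existing code and a few corrected sentences, with no extra patients for the correction itself. The downside is that the power stated for the stratified model may come out slightly less favourable.
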